### 3.9.4. Immunogenicity Endpoints

Immunogenicity evaluation endpoints include ADA.

### 3.9.5. Efficacy Endpoints

Efficacy evaluation endpoints include SELENA-SLEDAI score, PGA score, time from randomization to first SLE flare, prednisone dosage, BILAG-2004 score, 24-hour urine protein quantification (only for subjects whose urine protein/creatinine ratio exceeds the ULN during screening), urine protein/creatinine ratio (only for subjects whose urine protein/creatinine ratio exceeds the ULN during screening), IgG, IgA, IgM, IgE, anti-ds-DNA antibody, complement (C3, C4), CRP, ESR, etc.

### 3.10. End of Study

Under normal circumstances, the study will be considered completed when the last subject completes the last visit. The sponsor, Ethics Committee (EC), or other regulatory authorities may also terminate the study before its completion.

### **3.11. Actions in Case of Study Interruption Due to Natural Disasters or Public Health Events**

To ensure the rights and safety of subjects, compliance with Good Clinical Practice (GCP), and the integrity and continuity of the clinical study during natural disasters or public health events, the investigator or designated personnel may contact the sponsor to discuss the possibility of implementing appropriate risk mitigation plans, subject to the approval of the local health authorities, EC, or local government. These plans may include:

- Obtain informed consent or re-consent on risk mitigation.
- Perform re-screening for subjects who have been successfully screened, or extend the screening period.
- Perform home or remote visits (remote contact with subjects via telecommunication technology, including telephone, video, etc., for telemedicine visits) by qualified medical personnel.
- Complete routine examinations at an alternative institution (qualified local laboratory or imaging center, e.g., Grade II Level A hospital or above).
- IMP dispensation: For IMPs that can usually be self-administered, alternative safe methods for shipment may be adopted; for IMPs that are normally used only in a medical institution, an alternative plan for IMP administration will be communicated with regulatory authorities.

## 4. Study Procedures

### 4.1. Study Steps

#### 4.1.1. V1 (D-28 to D-1, Screening Period)

Subjects who sign the ICF should complete protocol-specified screening tests/assessments within 28 days prior to the first dose to determine their eligibility for enrollment.

Subjects will maintain a stable standard of care regimen for at least 30 days before the first dose of IMP. A stable standard of care regimen refers to the stable use of any of the following (alone or in combination): corticosteroids, antimalarials, NSAIDs, immunosuppressive or immunomodulatory agents, such as azathioprine, mycophenolate (including mycophenolate mofetil, mycophenolic sodium), methotrexate, leflunomide, tacrolimus, ciclosporin. [Note: Routine dose reduction of corticosteroids  $\leq 20$  mg/d prednisone (or equivalent dose of other corticosteroids) is also considered stable treatment]

All study procedures to be completed at screening are as follows:

- Obtain informed consent and sign ICF;
- Confirm eligibility according to inclusion/exclusion criteria;
- Collect demographic data: including age, sex, ethnicity, smoking history, alcohol consumption history, and menstrual history;
- Collect medical history, medication history, and surgical history: ① History of SLE: The date of SLE diagnosis should be recorded. ② SLE medication history: The medication use (including specific drugs/treatment, dosage, and usage, etc.) for at least 2 years prior to the screening visit should be recorded. ③ Medical history of other diseases: The occurrence of other diseases (including disease name and time of onset, etc.) within at least 6 months prior to the screening visit should be recorded. ④ Previous treatment history of other diseases: The treatment (including specific drugs/treatment, usage and dosage, etc.) within at least 1 month prior to the screening visit should be recorded. ⑤ Previous surgical history: The surgery (including name and date of surgery, etc.) within at least 6 months prior to the screening visit should be recorded.
- Measure body height and weight, and calculate body mass index (BMI);
- Perform infectious disease screening, including hepatitis b screening: hepatitis B five items (HBsAg, HBsAb, HBcAb, HBeAg, and HBeAb), and HBV-DNA if necessary; perform hepatitis c screening: HCV antibody, and HCV-RNA if necessary; HIV

- screening: HIV antibody; syphilis screening: treponema pallidum antibody;
- Chest X-ray: Chest X-ray (posteroanterior and lateral) should be performed, and additional tuberculosis screening-related tests may be added according to the site's diagnostic and treatment routine to rule out active pulmonary tuberculosis;
  - ANA;
  - Blood type and IAT: Blood type and IAT, including ABO, Rh, and IAT, must be performed during the screening period, and subjects will be provided with an identification card indicating their blood type and IAT information;
  - Vital signs: including temperature, pulse, respiration, and blood pressure;
  - Physical examination: including head and face, eyes, ears, nose and throat, oral cavity, skin, lymph nodes, respiratory system, cardiovascular system, abdomen, genitourinary system (if necessary), musculoskeletal system, nervous system, and mental status;
  - 12-lead ECG: including heart rate, PR interval, QRS duration, QT interval, and QTcF;
  - Laboratory test: including hematology, blood chemistry, urinalysis and coagulation function;
  - Blood pregnancy test (for women of childbearing potential only);
  - Urine protein/creatinine ratio, 24-hour urine protein (only for subjects whose urine protein/creatinine ratio exceeds the ULN during the screening period);
  - Immunology-related endpoints: including IgG, IgA, IgM, IgE, complement (C3, C4), anti-ds-DNA antibody, tested by the laboratories of each study site;
  - CRP, ESR tests;
  - SELENA-SLEDAI score;
  - PGA score;
  - Collection of prednisone dosage;
  - Recording of AEs;
  - Recording of concomitant therapies.

#### **4.1.2. Treatment Period (D1 to D57)**

The treatment period will last for 8 weeks. Subjects will complete baseline examinations at the baseline visit (D1) (safety laboratory tests before the first dose, including pregnancy test, can be completed on D1 or within 48 hours before D1), and the eligibility will be verified based on the inclusion/exclusion criteria (laboratory test results from the screening period can be used for eligibility verification). Eligible subjects will be enrolled in the study.

During the treatment period, subjects will receive intravenous infusions of the corresponding dose of CM313 or an equal volume of placebo according to the corresponding dosing frequency based on their assigned dose level.

During the treatment period, subjects will complete PK, PD, and immunogenicity blood sample collection according to the time points specified in Table 2.

During the treatment period, subjects should also complete safety tests/assessments and efficacy evaluations at the time points specified in the protocol.

#### **4.1.2.1. V2 (D1, baseline visit)**

- Verify eligibility based on the inclusion/exclusion criteria;
- Measure body weight;
- ANA: If laboratory test results are available within 3 days before the first dose of IMP, the test does not need to be repeated;
- Vital signs: including temperature, pulse, respiration, and blood pressure;
- Physical examination: including head and face, eyes, ears, nose and throat, oral cavity, skin, lymph nodes, respiratory system, cardiovascular system, abdomen, genitourinary system (if necessary), musculoskeletal system, nervous system, and mental status;
- 12-lead ECG: including heart rate, PR interval, QRS duration, QT interval, and QTcF;
- Laboratory tests: including hematology, blood chemistry, urinalysis, and coagulation function; if laboratory test results are available within 3 days before the first dose of IMP, the tests do not need to be repeated;
- Pregnancy test (for women of childbearing potential only): blood pregnancy test or urine pregnancy test, can be completed on D1 or within 48 hours before D1;
- Urine protein/creatinine ratio, 24-hour urine protein: can be completed on D1 or within 48 hours before D1. If test results are available within 3 days before the first dose of IMP, the tests do not need to be repeated; 24-hour urine protein test is only required for subjects whose urine protein/creatinine ratio exceeds the ULN during the screening period;
- Immunology-related endpoints: including IgG, IgA, IgM, IgE, complement (C3, C4), anti-ds-DNA antibody, tested by the central laboratory. The results of IgG, IgA, IgM, and IgE will not be provided to each study site before unblinding to avoid breaking the blindness;

- CRP, ESR: test results within 3 days before the first dose are acceptable. Baseline examinations can be completed on D1 or within 48 hours before D1;
- SELENA-SLEDAI score: If test results are available within 3 days before the first dose of IMP, the test does not need to be repeated;
- BILAG-2004 score: If test results are available within 3 days before the first dose of IMP, the test does not need to be repeated;
- PGA score: If test results are available within 3 days before the first dose of IMP, the test does not need to be repeated;
- SLE flare assessment;
- Randomization;
- IMP administration;
- PK, PD, and immunogenicity blood sampling. Please refer to Table 2 for specific sampling time points;
- Collection of prednisone dosage;
- Recording of AEs;
- Recording of concomitant therapies;
- Distribution of subject diary cards and training of subjects on how to fill them out.

#### **4.1.2.2. V3 (D8±1d)**

- Vital signs: including temperature, pulse, respiration, and blood pressure;
- Physical examination: including head and face, eyes, ears, nose and throat, oral cavity, skin, lymph nodes, respiratory system, cardiovascular system, abdomen, genitourinary system (if necessary), musculoskeletal system, nervous system, and mental status;
- 12-lead ECG: including heart rate, PR interval, QRS duration, QT interval, and QTcF;
- Laboratory test: including hematology, blood chemistry, urinalysis and coagulation function;
- PK, PD, and immunogenicity blood sampling. Please refer to Table 2 for specific sampling time points;
- Collection of prednisone dosage;
- Recording of AEs;
- Recording of concomitant therapies;
- Recovery and issuance of subject diary cards.

#### 4.1.2.3. V4 (D15±1d)

- Vital signs: including temperature, pulse, respiration, and blood pressure;
- Physical examination: including head and face, eyes, ears, nose and throat, oral cavity, skin, lymph nodes, respiratory system, cardiovascular system, abdomen, genitourinary system (if necessary), musculoskeletal system, nervous system, and mental status;
- 12-lead ECG: including heart rate, PR interval, QRS duration, QT interval, and QTcF;
- Laboratory test: including hematology, blood chemistry, urinalysis and coagulation function;
- Urine protein/creatinine ratio, 24-hour urine protein (only for subjects whose urine protein/creatinine ratio exceeds the ULN during the screening period);
- Immunology-related endpoints: including IgG, IgA, IgM, IgE, complement (C3, C4), anti-ds-DNA antibody, tested by the central laboratory. The results of IgG, IgA, IgM, and IgE will not be provided to each study site before unblinding to avoid breaking the blindness;
- CRP, ESR;
- SELENA-SLEDAI score;
- PGA score;
- SLE flare assessment;
- PK, PD, and immunogenicity blood sampling. Please refer to Table 2 for specific sampling time points;
- Collection of prednisone dosage;
- Recording of AEs;
- Recording of concomitant therapies;
- Recovery and issuance of subject diary cards.

#### 4.1.2.4. V5 (D22±1d)

- Vital signs: including temperature, pulse, respiration, and blood pressure;
- Physical examination: including head and face, eyes, ears, nose and throat, oral cavity, skin, lymph nodes, respiratory system, cardiovascular system, abdomen, genitourinary system (if necessary), musculoskeletal system, nervous system, and mental status;
- 12-lead ECG: including heart rate, PR interval, QRS duration, QT interval, and QTcF;

- Laboratory test: including hematology, blood chemistry, urinalysis and coagulation function;
- PK, PD, and immunogenicity blood sampling. Please refer to Table 2 for specific sampling time points;
- Collection of prednisone dosage;
- Recording of AEs;
- Recording of concomitant therapies;
- Recovery and issuance of subject diary cards.

#### **4.1.2.5. V6 (D29±1d)**

- Measure body weight;
- Vital signs: including temperature, pulse, respiration, and blood pressure;
- Physical examination: including head and face, eyes, ears, nose and throat, oral cavity, skin, lymph nodes, respiratory system, cardiovascular system, abdomen, genitourinary system (if necessary), musculoskeletal system, nervous system, and mental status;
- 12-lead ECG: including heart rate, PR interval, QRS duration, QT interval, and QTcF;
- Laboratory test: including hematology, blood chemistry, urinalysis and coagulation function;
- Pregnancy test (for women of childbearing potential only): blood or urine pregnancy test;
- Urine protein/creatinine ratio, 24-hour urine protein (only for subjects whose urine protein/creatinine ratio exceeds the ULN during the screening period);
- Immunology-related endpoints: including IgG, IgA, IgM, IgE, complement (C3, C4), anti-ds-DNA antibody, tested by the central laboratory. The results of IgG, IgA, IgM, and IgE will not be provided to each study site before unblinding to avoid breaking the blindness;
- CRP, ESR;
- SELENA-SLEDAI score;
- BILAG-2004 score;
- PGA score;
- SLE flare assessment;
- IMP administration;
- PK, PD, and immunogenicity blood sampling. Please refer to Table 2 for specific

sampling time points;

- Collection of prednisone dosage;
- Recording of AEs;
- Recording of concomitant therapies;
- Recovery and issuance of subject diary cards.

#### **4.1.2.6. V7 (D36±1d)**

- Measure body weight;
- Vital signs: including temperature, pulse, respiration, and blood pressure;
- Physical examination: including head and face, eyes, ears, nose and throat, oral cavity, skin, lymph nodes, respiratory system, cardiovascular system, abdomen, genitourinary system (if necessary), musculoskeletal system, nervous system, and mental status;
- 12-lead ECG: including heart rate, PR interval, QRS duration, QT interval, and QTcF;
- Laboratory test: including hematology, blood chemistry, urinalysis and coagulation function;
- IMP administration;
- PK, PD, and immunogenicity blood sampling. Please refer to Table 2 for specific sampling time points;
- Collection of prednisone dosage;
- Recording of AEs;
- Recording of concomitant therapies;
- Recovery and issuance of subject diary cards.

#### **4.1.2.7. V8 (D43±1d)**

- Measure body weight;
- Vital signs: including temperature, pulse, respiration, and blood pressure;
- Physical examination: including head and face, eyes, ears, nose and throat, oral cavity, skin, lymph nodes, respiratory system, cardiovascular system, abdomen, genitourinary system (if necessary), musculoskeletal system, nervous system, and mental status;
- 12-lead ECG: including heart rate, PR interval, QRS duration, QT interval, and QTcF;
- Laboratory test: including hematology, blood chemistry, urinalysis and coagulation function;

- Urine protein/creatinine ratio, 24-hour urine protein (only for subjects whose urine protein/creatinine ratio exceeds the ULN during the screening period);
- Immunology-related endpoints: including IgG, IgA, IgM, IgE, complement (C3, C4), anti-ds-DNA antibody, tested by the central laboratory. The results of IgG, IgA, IgM, and IgE will not be provided to each study site before unblinding to avoid breaking the blindness;
- CRP, ESR;
- SELENA-SLEDAI score;
- PGA score;
- SLE flare assessment;
- IMP administration;
- PK, PD, and immunogenicity blood sampling. Please refer to Table 2 for specific sampling time points;
- Collection of prednisone dosage;
- Recording of AEs;
- Recording of concomitant therapies;
- Recovery and issuance of subject diary cards.

#### **4.1.2.8. V9 (D50±1d)**

- Measure body weight;
- Vital signs: including temperature, pulse, respiration, and blood pressure;
- Physical examination: including head and face, eyes, ears, nose and throat, oral cavity, skin, lymph nodes, respiratory system, cardiovascular system, abdomen, genitourinary system (if necessary), musculoskeletal system, nervous system, and mental status;
- 12-lead ECG: including heart rate, PR interval, QRS duration, QT interval, and QTcF;
- Laboratory test: including hematology, blood chemistry, urinalysis and coagulation function;
- IMP administration;
- PK, PD, and immunogenicity blood sampling. Please refer to Table 2 for specific sampling time points;
- Collection of prednisone dosage;
- Recording of AEs;
- Recording of concomitant therapies;

- Recovery and issuance of subject diary cards.

#### **4.1.2.9. V10 (D57±1d, EOT visit)**

- Measure body weight;
- Vital signs: including temperature, pulse, respiration, and blood pressure;
- Physical examination: including head and face, eyes, ears, nose and throat, oral cavity, skin, lymph nodes, respiratory system, cardiovascular system, abdomen, genitourinary system (if necessary), musculoskeletal system, nervous system, and mental status;
- 12-lead ECG: including heart rate, PR interval, QRS duration, QT interval, and QTcF;
- Laboratory test: including hematology, blood chemistry, urinalysis and coagulation function;
- Pregnancy test (for women of childbearing potential only): blood or urine pregnancy test;
- Urine protein/creatinine ratio, 24-hour urine protein (only for subjects whose urine protein/creatinine ratio exceeds the ULN during the screening period);
- Immunology-related endpoints: including IgG, IgA, IgM, IgE, complement (C3, C4), anti-ds-DNA antibody, tested by the central laboratory. The results of IgG, IgA, IgM, and IgE will not be provided to each study site before unblinding to avoid breaking the blindness;
- CRP, ESR;
- SELENA-SLEDAI score;
- BILAG-2004 score;
- PGA score;
- SLE flare assessment;
- PK, PD, and immunogenicity blood sampling. Please refer to Table 2 for specific sampling time points;
- Collection of prednisone dosage;
- Recording of AEs;
- Recording of concomitant therapies;
- Recovery and issuance of subject diary cards.

#### **4.1.3. Follow-up Period (D58 to D113)**

After the treatment period, subjects will enter an 8-week follow-up period.

Subjects will return to the study site for visits at the times specified in the protocol to undergo safety tests/assessments, efficacy evaluations, and continue to provide PK, PD, and

immunogenicity samples until the EOS visit is completed at the end of follow-up. If clinically significant abnormalities are identified, the investigator will determine whether the subject needs to undergo reexamination, treatment, or hospitalization observation and the subject will be followed up until recovery or stabilized outcome.

#### **4.1.3.1. V11 (D71±3d), V12 (D85±3d), V13 (D99±3d)**

- Measure weight (only at V12, not at V11 or V13);
- Vital signs: including temperature, pulse, respiration, and blood pressure;
- Physical examination: including head and face, eyes, ears, nose and throat, oral cavity, skin, lymph nodes, respiratory system, cardiovascular system, abdomen, genitourinary system (if necessary), musculoskeletal system, nervous system, and mental status;
- 12-lead ECG: including heart rate, PR interval, QRS duration, QT interval, and QTcF;
- Laboratory test: including hematology, blood chemistry, urinalysis and coagulation function;
- Pregnancy test (for women of childbearing potential only) (only at V12, not at V11 or V13): blood or urine pregnancy test;
- Urine protein/creatinine ratio, 24-hour urine protein (only for subjects whose urine protein/creatinine ratio exceeds the ULN during the screening period);
- Immunology-related endpoints: including IgG, IgA, IgM, IgE, complement (C3, C4), anti-ds-DNA antibody, tested by the central laboratory. The results of IgG, IgA, IgM, and IgE will not be provided to each study site before unblinding to avoid breaking the blindness;
- CRP, ESR;
- SELENA-SLEDAI/PGA score;
- SLE flare assessment;
- BILAG-2004 score (only at V12, not at V11 or V13);
- PK, PD, and immunogenicity blood sampling. Please refer to Table 2 for specific sampling time points;
- Collection of prednisone dosage;
- Recording of AEs;
- Recording of concomitant therapies;
- Recovery and issuance of subject diary cards.

#### 4.1.3.2. V14 (D113±3d, EOS visit)

- Measure body weight;
- Chest X-ray: posteroanterior and lateral position;
- ANA;
- Vital signs: including temperature, pulse, respiration, and blood pressure;
- Physical examination: including head and face, eyes, ears, nose and throat, oral cavity, skin, lymph nodes, respiratory system, cardiovascular system, abdomen, genitourinary system (if necessary), musculoskeletal system, nervous system, and mental status;
- 12-lead ECG: including heart rate, PR interval, QRS duration, QT interval, and QTcF;
- Laboratory test: including hematology, blood chemistry, urinalysis and coagulation function;
- Pregnancy test (for women of childbearing potential only): blood pregnancy test;
- Urine protein/creatinine ratio, 24-hour urine protein (only for subjects whose urine protein/creatinine ratio exceeds the ULN during the screening period);
- Immunology-related endpoints: including IgG, IgA, IgM, IgE, complement (C3, C4), anti-ds-DNA antibody, tested by the central laboratory. The results of IgG, IgA, IgM, and IgE will not be provided to each study site before unblinding to avoid breaking the blindness;
- CRP, ESR;
- SELENA-SLEDAI score;
- BILAG-2004 score;
- PGA score;
- SLE flare assessment;
- PK, PD, and immunogenicity blood sampling. Please refer to Table 2 for specific sampling time points;
- Collection of prednisone dosage;
- Recording of AEs;
- Recording of concomitant therapies;
- Collection of subject diary cards.

## **4.2. Dose Interruption**

During the treatment period, if the IMP is interrupted for a subject due to an AE or other reasons, the investigator may consider resumption of the IMP, directly discontinue the treatment or even withdraw from the study on a case-by-case basis. If the resumption of dosing is considered, relevant discussions should be held with the sponsor's medical monitor.

## **4.3. Early Withdrawal from the Study**

If a subject withdraws from the study early, they should complete the "early withdrawal" visit as far as possible. The specific procedures, examinations, and assessments will be the same as those of the EOS visit, and blood samples for PK, PD, and immunogenicity will be collected. The sample collection time or safety examination time should be close to the time of withdrawal from the study as far as possible. At the "early withdrawal" visit, procedures, examinations and assessments will be waived if there are results within 3 days. Subjects who withdraw from the study early may be replaced following discussion between the investigator and the sponsor.

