**Early Withdrawal from the Study**

If a subject withdraws early from the study, the "early withdrawal" visit should be completed and blood samples for PK, PD, and immunogenicity should be collected. The procedures, examinations and assessments required for early withdrawal visit are the same as those for the EOS visit, and the sample collection time or safety examination time should be as close as possible to the time of withdrawal from the study.

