### **Treatment Period (8 weeks)**

The treatment period includes a single-dose phase (Day 1 to Day 28) and a multiple-dose phase (Day 29 to Day 57). Successfully enrolled participants will be randomized prior to the first dose administration and will receive the corresponding dose of CM313 or placebo via intravenous infusion according to their assigned dose level. Subjects will be observed for 28 days (single-dose phase) after the first dose (D1). After the safety and tolerability are assessed as acceptable by the investigator, subjects will enter the multiple-dose phase and receive four consecutive doses (QW) of the investigational medicinal product (IMP). The administration of the next dose level can be initiated after completion of the single-dose phase in the previous dose level and that there are no AEs meeting the dose escalation interruption and stopping criteria as evaluated by the investigator and the sponsor. The details are as follows:

- **Dose Levels:** Four dose levels are planned: 2 mg/kg, 4 mg/kg, 8 mg/kg, and 16 mg/kg.
- **Number of Subjects:** Each dose level will include 10 subjects (8 subjects will receive CM313, and 2 subjects will receive placebo).
- **Route and Frequency of Administration:**

Both CM313 and placebo will be administered intravenously.

  - **Single-dose phase (D1 to D28):** On D1, subjects will receive the corresponding dose of CM313 or placebo according to their assigned dose level via intravenous infusion. Following administration, they will enter a 28-day safety observation period.
  - **Multiple-dose phase (D29-D57):** On D29, subjects will enter the multiple-dose phase and receive the corresponding dose of CM313 or placebo via intravenous infusion, once weekly (QW), for a total of 4 doses. After completing all doses, subjects will have an end of treatment (EOT) visit 1 week after the last dose.
- **Dose Escalation:** The next dose level can be initiated after all subjects at the previous dose level have completed D1-D28 safety observation without any AEs

meeting the interruption and stopping criteria for dose escalation as judged by the investigator and the sponsor.

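### The 3-day waiver at the early-withdrawal visit does not require results taken after the last infusion or the event, so infusion-day values can replace the withdrawal tests (minor)

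*Protocol*

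**What the plan says.** Three places in the protocol describe the early-withdrawal visit.

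- **Section 4.3** gives it the same content as the EOS visit and says that "blood samples for PK, PD, and immunogenicity will be collected". It asks for timing near the departure: "The sample collection time or safety examination time should be close to the time of withdrawal from the study as far as possible". It then says that "procedures, examinations and assessments will be waived if there are results within 3 days".
- **Table 1, note 1** repeats the waiver in the same words and adds no condition.
- **The synopsis** (Early Withdrawal from the Study) describes the same visit and asks that the "safety examination time should be as close as possible to the time of withdrawal from the study". It contains no waiver.

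The waiver is worded as a rule, not as an option for the investigator. It is tied only to the age of the earlier result. Other 3-day allowances in the protocol are tied to dosing. At V2, for example, section 4.1.2.1 says of the safety laboratory tests that "if laboratory test results are available within 3 days before the first dose of IMP, the tests do not need to be repeated".

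**The concern.** The early-withdrawal visit exists to obtain a last set of measurements from a subject who is leaving, possibly because something went wrong after an infusion. A look-back defined only by elapsed days can be met by results taken before that infusion or before that event. Applied literally, the rule can then remove the measurements that would show the subject's state after the event.

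Safety is the primary endpoint, and each dose level has only 8 subjects on CM313 and 2 on placebo. Laboratory and ECG findings are analysed as shifts from baseline to post-baseline (sections 8.3.8.3 and 8.3.8.6), and section 8.3.12 says missing safety data will not be handled. A subject with no post-baseline value cannot contribute to those tables. If the departure was caused by acute toxicity, that absence would not be random.

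**Working it through.** There is no plan figure to reproduce. The check is a reading of the schedule and a count of days.

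**Inputs (Table 1; sections 4.1.2 and 5.2)**
- Infusions: D1, D29, D36, D43, D50.
- Safety set (vital signs, physical examination, ECG, laboratory tests): every visit, including each infusion day. The V8 list, for example, has "Laboratory test: including hematology, blood chemistry, urinalysis and coagulation function".
- Next scheduled visit after each infusion: D8, D36, D43, D50, D57.
- Visit windows: none for D1, ±1 day for V3 to V10.

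**Step 1. Is a scheduled safety set available 1 to 3 days after an infusion?** Nominal gaps are 8 − 1 = 7, 36 − 29 = 7, 43 − 36 = 7, 50 − 43 = 7 and 57 − 50 = 7 days. With windows at their worst, the gap is (8 − 1) − 1 = 6 days after D1 and, for example, (36 − 1) − (29 + 1) = 5 days in the weekly phase. All exceed 3, so the answer is no. Table 2 schedules some PK and PD samples at 24 and 72 hours after certain doses, but these are not safety tests.

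**Step 2. How many days are affected?** Days 1 to 3 after each infusion are D2–D4, D30–D32, D37–D39, D44–D46 and D51–D53.
- 5 × 3 = 15 days; 15 / 57 = 26%.
- Counting the infusion days as well: 20 / 57 = 35%.

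The smaller figure is the relevant one, because on those 15 days the only scheduled results inside the look-back are from the infusion visit.

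**Step 3. The D1 case.** Section 4.1.2 has baseline examinations completed and eligibility verified before the subject is enrolled, so these results are pre-dose.
- A result taken on D1 satisfies the waiver on D2, D3 and D4.
- A laboratory result taken x days before D1 satisfies it for 3 − x days after D1. With x from 0 to 3, D1 contributes 3 to 0 days, and the laboratory total is 15 to 12 of 57 days (26% to 21%). Section 4.1.2.1 gives no such early allowance for the ECG, so 15 stands there.
- The next scheduled set is V3 (D8). A subject leaving on D2 to D4 can therefore have no post-baseline laboratory or ECG value. One leaving on D5 to D7 has baseline results more than 3 days old and must be tested. The earlier departure yields less data.

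**Step 4. V6 to V9.** The protocol does not say whether the tests precede the infusion. If they do, the accepted values predate the last dose. If they do not, they can still predate a later event. These subjects have scheduled post-baseline values from earlier visits, so the possible loss is the latest value, not every value.

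**Step 5. Which other assessments can be waived?** SELENA-SLEDAI, PGA and flare assessment are scheduled at V2, V6 and V8, with CRP/ESR, immunology and urine protein tests; BILAG-2004 is at V2 and V6. None is scheduled at V7 or V9. The efficacy loss can therefore arise only after D1, D29 and D43 (9 of the 15 days). Chest X-ray is not done at any infusion visit, nor ANA at V6 to V9, so those cannot be waived by an infusion-visit result.

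**The case against.** The strongest reply is that the path is narrow and largely covered elsewhere.

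- **Only study withdrawal is affected.** A subject who stops IMP but stays in the study is asked to complete the EOT and follow-up visits as far as possible (section 3.8.7). Permanent discontinuation after an infusion reaction (section 3.8.2.4) is a treatment decision. This stands.
- **Events are captured without the visit tests.** AEs are collected to the end of follow-up and tracked past the last visit if needed (6.1.2), and SAEs unresolved at early withdrawal must be followed (6.2.2). This stands, and it protects the AE part of the primary endpoint.
- **Extra tests are possible.** Sections 5.2.1 to 5.2.4 allow them and section 4.4 allows unscheduled visits. This stands only in part: they are discretionary, and section 4.4 requires only clinically significant unscheduled results to be recorded in the CRF.
- **A 3-day look-back is compatible with timing close to withdrawal.** This is fair. The text is silent on the last infusion; it does not contradict itself.

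Four stronger readings might tempt a reader, and the protocol does not support them.

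- Infusion reactions occurred in 5 of 10 subjects in CM313MM001, which might suggest frequent losses. That is a reaction rate. Section 1.3.2 reports 3 subjects stopping for progression, 1 withdrawing voluntarily and 6 still on treatment, and none leaving because of a reaction.
- The V6 to V9 lists put safety tests ahead of IMP administration, which might suggest pre-dose timing. The same lists put PK sampling after administration, although Table 2 requires a pre-dose sample, so list order shows nothing.
- A flare before departure might be thought to be censored as flare-free. The protocol states no such rule; censoring would belong to the SAP, which is not available here.
- The loss might be expressed as a share of last-value safety data. No last-value analysis is planned.

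**Conclusion.** The waiver is unconditional in both places. Read literally, it lets infusion-day results replace the withdrawal tests for a subject who leaves the study 1 to 3 days after dosing. The exposed interval is 15 of 57 treatment-period days (26%; 12 to 15 days for laboratory tests, depending on when baseline samples were drawn). This is a count of calendar days, not a probability of withdrawal, and the protocol gives no basis for estimating how many subjects would be affected.

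The consequence is firmest after D1, where the results are pre-dose and no post-baseline laboratory or ECG value may exist. After later infusions it is conditional on timing that the protocol does not state. In all cases it assumes that the rule is followed as written and that no unscheduled test is recorded. The loss is limited to measured safety values and, after D1, D29 and D43, to the efficacy assessments done at those visits. AE and SAE ascertainment is not removed. Severity: minor.

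**What to change.** In section 4.3 and Table 1 note 1, allow an assessment to be waived only when the result from the previous 3 days was obtained after the most recent IMP infusion and after the onset of any event leading to withdrawal. Align the synopsis, which currently omits the waiver, so that all three places describe the same visit.

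The cost is one sentence in two places plus the synopsis alignment, and one repeat set of standard tests in the few subjects who withdraw within 3 days of an infusion, at a visit the protocol already asks for. No sample size, endpoint or analysis changes.
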